### Sample size

To calculate the sample size, we believe that the educational group intervention can increase the proportion of mother/infant pairs that use EBF at six months by 15%. Assuming that 24% of mothers use EBF at six months (National Health Survey (2006). National Statistics Institute http://www.ine.es), a type I error of 5% and a strength of 80%, we need a sample of 150 mother/infant pairs in each group. As this is a randomized design with conglomerates (each conglomerate is a health centre), the sample size needs to be increased taking into account the effect of the design (ED = 1+ (ñ-1)*CCI, where ñ is the average size of each cluster and CCI is the intra-class coefficient of correlation).

Considering a CCI of 0.01 and an average size of 30 pairs per centre, the effect of the design is 1.29. Taking this data into account, the sample size increases to 194 pairs in each group. If we then take into account the loss rate of 10%, the total size surpasses 432 pairs (216 for each branch).

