### Prevalence of breast-feeding in developed countries: Associated factors

In spite of the broad dissemination of recommendations to promote EBF and its benefits, only 35% of newborns around the world receive EBF after the first three or four months of life [15]. The rates are much lower than those set out by the WHO in European countries, and specifically, in Spain the rates are similar to the rest of the developed countries, with 24.72% EBF at six months, and slightly lower in the Region of Madrid (23.54%) [16].

In Spain the average length of breastfeeding is around 3–5 months. The greater number of abandonments of EBF takes place during the first 4 weeks, (sometimes up to one third of cases) and between the 3rd and 4th months of life, which coincides with the imminent return of the mother to work [17–20].

According to the results of an observational study in Spain the factors that influence the continuity of EBF up to six months are diverse: lack of confidence to breast-feed, pain, suction problems, cracks, infections, ingurgitation, mastitis, baby crying, type of birth, execution of early skin to skin contact, bad experience with prior breast-feeding, comments by family members and/or friends, aspects related with going back to work, and the socio-economic and education level of the mother [21, 22]. Other authors point out the possible effect that the model of the breast-feeding mothers’ mothers, women that lived during periods of setbacks regarding the prevalence of breast-feeding, many of whom most likely did not breast-feed, could have on the breast-feeding mother’s [14].

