### Subjects of the study

Mother-infant pairs using EBF, that seek care or information at any PHC consultation before the first month of life of the newborn and that give their consent to participate in the study.

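### The 24% control rate describes mothers in general, not the pairs still in EBF who are enrolled; power for +15 points is then somewhat below the stated 80%

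*Protocol article*

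**What the plan says.** The Sample size section takes its control rate from a national survey of 2006: "Assuming that 24% of mothers use EBF at six months". The figure agrees with the rates that the Background reports for the country and the region: "with 24.72% EBF at six months, and slightly lower in the Region of Madrid (23.54". The intervention is expected to raise the six-month proportion: "can increase the proportion of mother/infant pairs that use EBF at six months by 15" per cent. The section then states "a type I error of 5% and a strength of 80%, we need a sample of 150 mother/infant pairs in each group", and for clustering "Considering a CCI of 0.01 and an average size of 30 pairs per centre, the effect of the design is 1.29". This gives 194 per group, and 216 per group (432 in total) after 10% loss.

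Eligibility is narrower than the survey population. Subjects of the study admits "Mother-infant pairs using EBF, that seek care or information at any PHC consultation before the first month of life of the newborn". The Inclusion criteria require EBF at the selection visit and an infant no older than 4 weeks, and the Abstract requires EBF within the previous 24 hours. The Background describes the timing of abandonment: "The greater number of abandonments of EBF takes place during the first 4 weeks, (sometimes up to one third of cases"). The Sample size section makes no adjustment for this selection.

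**The concern.** The control rate that matters for sizing is the probability of EBF at six months given EBF at entry. The planning rate appears to be unconditional. Its denominator, as worded, is mothers, so it would include those who never used EBF or had stopped before a selection visit could take place. Conditioning on EBF at entry removes mothers who count as failures in the survey and leaves the successes in, so the conditional rate must be higher whenever anyone has stopped or never started before entry. The article's own Background says that early stopping is common.

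Two things follow. First, moving the control rate up from 24% towards the middle of the scale increases the binomial variance, so a fixed 15-point difference is detected with less power than stated. Second, 24% becomes a poor benchmark for the control arm. The Discussion worries about highly motivated control centres. A control arm well above 24% could be put down to that when selection at entry alone would produce it.

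**Working it through.** **Inputs (Sample size section).** Control rate 24%; increase 15; type I error 5%; power 80%; ICC 0.01; 30 pairs per centre; loss 10%.

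**Step 1: reproduce the plan.** Normal approximation for two proportions, two-sided 5%, no continuity correction:

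n = [1.96·√(2p̄(1−p̄)) + 0.8416·√(p₁(1−p₁) + p₂(1−p₂))]² / (p₂−p₁)²

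- With p₁ = 0.24, p₂ = 0.39 and p̄ = 0.315: n = 149.4, so 150 per group.
- Design effect: 1 + 29 × 0.01 = 1.29; 150 × 1.29 = 193.5, so 194.
- Loss: 194 / 0.9 = 215.6, so 216 per arm and 432 in total.

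The plan reproduces exactly. Reading 15% as a relative increase (24% to 27.6%) would need 2,318 per group, so the plan was sized on 15 percentage points.

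**Step 2: power when only the control rate changes.** Keep the plan's own design effect. The effective size per group is 194 / 1.29 = 150.4.

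Power = Φ{[0.15·√150.4 − 1.96·√(2p̄(1−p̄))] / √(p₁(1−p₁) + p₂(1−p₂))}

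- At 24%: (1.8395 − 1.2875) / 0.6483 = 0.851, power 80.3%.
- At 36%: (1.8395 − 1.3741) / 0.6930 = 0.672, power 74.9%.

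| Control rate (assumed, except 24%) | Intervention rate | Power | Total pairs for 80% |
|---|---|---|---|
| 24% (plan) | 39% | 80.3% | 432 |
| 28% | 43% | 77.9% | 458 |
| 32% | 47% | 76.1% | 478 |
| 36% | 51% | 74.9% | 492 |
| 42.5% | 57.5% | 74.2% | 500 |

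The last row is the minimum, because the two rates are then symmetric about 50%. Power returns to 80.3% only at a control rate of 61% (61% v 76% mirrors 24% v 39%). Any control rate between 24% and 61% therefore lowers power for +15 points.

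**Step 3: where 32% and 36% come from.** They are illustrations that use the Background's one third.

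- If one third of mothers stop before entry: 24 / (1 − 1/3) = 36%.
- If one third of all abandonments occur before entry: 24 / (1 − 0.76/3) = 24 / 0.747 = 32%.

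Both assume that every mother started EBF and that every pair enters after the early losses. Neither assumption is in the document.

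**Step 4: the same check on another effect scale.** The odds ratio implied by 24% to 39% is (0.39/0.61) / (0.24/0.76) = 2.02. Held constant at a control rate of 36%, it gives 53.2% in the intervention arm and power of 85.6%. Holding the ratio 39/24 = 1.625 constant gives 58.5% and power of about 98%.

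**The case against.** The strongest reply is that the size of the shift cannot be known from this article. The one third is hedged as an upper figure, it may refer to mothers or to abandonments, and it comes from cited studies that are not at hand. The survey's denominator is inferred from its description as a rate of mothers. Pairs may enter at any age up to 4 weeks, so many still face the early losses after enrolment. All of this stands, and it means that no single corrected control rate can be asserted. It does not restore 24%, because the direction needs only that some mothers had stopped, or never started, before selection.

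The second reply is that the loss of power depends on the effect scale. That also stands: on an odds-ratio or ratio scale a higher control rate raises power. But the plan was sized on an absolute difference, and the stated 80% belongs to that target.

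A reader might also infer more than the documents support.

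- **That the true rate lies between 24% and 36%.** It is not bounded so. Removing never-starters and the preterm, low-birth-weight and clinical exclusions could push it above 36%.
- **That the control rate is close to 50%.** Nothing in the article leads there; its own abandonment figure gives 32–36% under the assumptions in the working.
- **That power falls well below 74%.** The control rate alone cannot do that. Ten centres for 432 pairs is 43.2 per centre instead of 30, and few clusters mean few degrees of freedom. Both reduce power further, but they do so at 24% as well and are a separate matter.

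**Conclusion.** The point holds as a minor planning error. The control rate does not describe the enrolled cohort, and the stated 80% power for +15 points rests on it. With the plan's own design effect and loss allowance, power for that difference is about 78% at 28%, 76% at 32% and 75% at 36%, with a floor of about 74%. The worst case is about 6 points of power, or 500 pairs instead of 432.

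This rests on three things: the survey rate covering mothers regardless of EBF status in the first weeks, which its wording suggests but does not prove; the effect being 15 absolute points, which is the reading that reproduces 150; and control rates above 24% that are assumed, since the document gives none. It does not show that the trial is underpowered for the effect it will actually meet. If the benefit is better described by a constant odds ratio, power at 36% is about 86%.

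**What to change.** In the Sample size section:

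1. Define the control rate as the proportion in EBF at six months among pairs in EBF at enrolment.
2. Label whatever value or range is used, for example 28–42%, as an assumption. Cite the Background's early-abandonment statement as the reason it exceeds the survey rate, and do not present any end of the range as a bound.
3. State that 15% means absolute percentage points.
4. Replace the 80% with the power for that difference over the range: about 74–78% for 432 pairs and a design effect of 1.29.

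The cost is one revised paragraph and a slightly less favourable stated power. Restoring 80% at the planned design effect would take 458 pairs at 28% and up to 500 at about 42%. That is a choice for the sponsor and is not needed to correct the statement.

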### Design of the study

This study is a community, multicentre, parallel clinical trial, randomised by clusters, that compares usual care and an education strategy performed by primary healthcare professionals. The intervention will be carried out with mother-infant pairs in ten PHCCs in the Community of Madrid (Spain).

The randomization units will be the PHCCs (clusters). The units of analysis are the mother-infant pairs attended to by the PHCCs. This design by clusters minimises possible contamination effects between centres.

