### Statistical analysis

The database will be filtered before the statistical analysis is performed to improve the quality of the data collected. The use of the design by conglomerates will be taken into account in all phases of the analysis, especially when calculating the confidence intervals of the estimations and in the hypothesis tests. The following will be carried out:

1. Descriptive analysis of the demographic and baseline characteristics of the subjects of both groups. The quantitative variables will be described by their measurements of central, mean or median tendencies, in the case of asymmetrical distributions, and their measurements of dispersion, typical deviation or interquartile amplitude, respectively. The qualitative variables will be described by their proportion and confidence interval.

2. Initial comparability study of the two groups regarding their baseline characteristics, response variables and prognostic factors. The Student t test or the Mann-Whitney test will be used if the normality hypothesis is rejected for the data. If the study variables are qualitative, the Pearson’s Chi-squared test or Fisher’s exact test will be used, when applicable. In the case of inequality, the possible confounding factors will be defined by which the final analysis of the principal variable of effectiveness will be adjusted.

3. Principal analysis of effectiveness. The effect of the PROLACT intervention in the principal response variable: a comparison will be made of the proportion of mother/child pairs using EBF at six months in both groups, using Fisher’s exact test, while also estimating the confidence interval for the difference. If the confounding factors were distributed in an unequal manner in each group, a model will be constructed of explicative logistical regression where the dependent variable will be EBF at six months and the independent variable will be “treatment” group adjusted for the possible confounding factors. The analysis of effectiveness will be done by intention-to-treat.

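### The stated 80% power treats the between-centre variance as known; with only ten centres it is about 67–70% for a centre-level t-test, and about 76–78% for less conservative cluster-adjusted tests

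*Protocol article*

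**What the plan says.** The Sample size section starts from a control rate ("Assuming that 24% of mothers use EBF at six months") and an intervention that "can increase the proportion of mother/infant pairs that use EBF at six months by 15" per cent. From these it states the requirement before clustering: "a type I error of 5% and a strength of 80%, we need a sample of 150 mother/infant pairs in each group". Clustering enters through one multiplier: "Considering a CCI of 0.01 and an average size of 30 pairs per centre, the effect of the design is 1.29". That gives 194 pairs per arm, and 216 after allowing for 10% loss.

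The number of centres is fixed under Design of the study: "The intervention will be carried out with mother-infant pairs in ten PHCCs in the Community of Madrid (Spain". The Randomisation section splits the centres into equal groups, so five per arm.

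The Statistical analysis section promises that "The use of the design by conglomerates will be taken into account in all phases of the analysis", with confidence intervals and hypothesis tests singled out. The same section then names Fisher's exact test for the primary comparison, an individual-level test with no adjustment for centre.

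**The concern.** A design effect enlarges the variance but leaves the critical value at 1.96, as though the between-centre variance were known or estimated from many centres. Here it must be estimated from ten. A test based on centre proportions has 10 − 2 = 8 degrees of freedom and a critical value of 2.306. The design effect does not pay for that difference.

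If the power is lower than printed, a non-significant result will be read against a chance of detection that the trial did not have. That matters because the Discussion looks ahead to extending the intervention to all healthcare centres. In the other direction, an analysis that ignores the small number of centres can run above the stated 5% type I error.

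**Working it through.** **Inputs.** Control 24%, intervention 39%, 5% type I error, 80% power, intra-class correlation (ICC) 0.01, 30 pairs per centre and 10% loss (Sample size); ten centres (Design of the study); equal groups (Randomisation). Neither the formula nor the sidedness is stated. Two-sided testing and normal quantiles are inferred because they reproduce 150 (one-sided gives 118; two-sided with continuity correction gives 163). The increase is read as absolute, since a relative 15% would need 2,318 per arm.

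**1. The plan's own figures.**
- n = [1.96·√(2·0.315·0.685) + 0.8416·√(0.24·0.76 + 0.39·0.61)]² / 0.15² = 149.4, so 150.
- Design effect = 1 + 29·0.01 = 1.29; 150·1.29 = 193.5, so 194; 194/0.9 = 215.6, so 216.

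The whole chain reproduces.

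**2. Power with 194 per arm and design effect 1.29.**
- SE = √(1.29·(0.1824 + 0.2379)/194) = 0.0529; noncentrality = 0.15/0.0529 = 2.84.
- Normal reference: 81.0% (80.3% with the pooled variance).
- Noncentral t, 8 df, critical value 2.306: 70.1% (69.0% pooled).
- Difference detectable with 80% power on 8 df: 17.0 points.

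**3. Cluster size implied by ten centres.** Ten centres of 30 give 300 pairs, not 388 (2·194) or 432. With 194 analysed per arm, each centre contributes 194/5 = 38.8, so the design effect is 1 + 37.8·0.01 = 1.378.
- SE = 0.0546; noncentrality = 2.75.
- Normal reference: 78.4%. t on 8 df: 67.3% (66.2% pooled). Beta-binomial simulation with 39 pairs per centre: about 67%.

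**4. No losses at all (216 per arm), t on 8 df.** 74.6% if the design effect is held at 1.29; 70.5% at the 43.2 pairs per centre that ten centres imply (design effect 1.422).

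**5. Other tests, by simulation (five centres per arm, 39 pairs each).**

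| Test | Setting | Type I error | Power |
|---|---|---|---|
| Individual-level, design effect estimated from the ten centres, referred to 1.96 | design effect 1.29 | 5.5% | about 78% |
| Same | ICC 0.01 | 5.8% | about 76% |
| Same | ICC 0.02 | 6.9% | – |
| Same | ICC 0.05 | 8.2% | – |
| Centre-level statistic referred to 1.96 | ICC 0.01 | 8.4–8.7% | about 77–78% |
| Centre-level statistic, t on 8 df | ICC 0.01 | about 5% | about 67% |

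**6. The named test.** An unadjusted large-sample comparison has type I error 2·[1 − Φ(1.96/√1.29)] = 8.4% at design effect 1.29, and 9.5% with 1.378 in place of 1.29. Fisher's exact test is conservative, so it lies lower: in a simulation of 40,000 trials with the same layout it gave 6.6% at design effect 1.29 and 7.8% at ICC 0.01. Both exceed 5%.

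**The case against.** The strongest reply is that 70% belongs to one test that the plan never names. The article names individual-level methods and promises to account for clustering. With an ICC near 0.01 most of the variance is binomial, so 8 df overstates the penalty for such methods. This stands: an individual-level test with an estimated design effect keeps about 76–78% power at close to the nominal error. A reader might infer that no cluster analysis holding 5% can come near 80%, or that using 1.96 necessarily pushes the error to about 8.7%. The documents do not support either. The 8.7% is specific to the centre-level statistic referred to 1.96. The milder result, however, depends on an assumed ICC, and the error rises as the ICC grows.

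Second, a design effect of 1.29 implies 30 pairs per centre, hence about 194/30 = 6.5 centres per arm, or 13 centres and 11 df. Until that is reconciled with ten centres, the degrees of freedom are not settled. This also stands as a criticism of the text, but it does not rescue the figure: 11 df gives 73.4%.

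Third, nothing is miscalculated, and the choice of reference distribution is commonly left to the analysis plan, which is not shown. Both points are fair. The missing detail is not itself the finding, and nothing says that the analysts will use 1.96 in a cluster-adjusted test. What remains is a printed power that the printed number of centres does not support, and a named primary test that does not meet the section's own commitment on clustering.

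**Conclusion.** The concern holds in a limited form. The sample-size arithmetic is correct for the method used, but the method makes no allowance for estimating between-centre variance from ten centres. Power for a 15-point difference is about 70% for a centre-level t-test on 8 df at design effect 1.29, and about 67% at the cluster size that ten centres imply. It is about 76–78% for an individual-level test with an estimated design effect, if the ICC is near 0.01 and a slightly raised type I error is accepted. Against the stated 80%, the shortfall is roughly 2 to 13 points, depending on the test and the cluster size. No test examined that estimates the between-centre variance reached 80%.

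It would be too strong to say that the trial simply has 70% power. That figure is conditional on the test. It also rests on two-sided testing, five centres per arm, equal cluster sizes, an ICC of 0.01 or a design effect of 1.29 as stated, and the planned 10% loss.

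**What to change.** Keep 432 pairs and ten centres.

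- **Sample size section:** reconcile the 30 pairs per centre with ten centres. Restate the power for a 15-point difference as about 67–70% with a t reference on 8 df, or state that 80% power applies to about 17 points at design effect 1.29. Name the test assumed in either case.
- **Statistical analysis section:** replace the unadjusted Fisher's exact test as the primary test with a cluster-adjusted test and confidence interval that use a small-sample reference. Options are t on 8 df for centre-level proportions, or a mixed or GEE model with a small-sample correction.

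The change is one of wording and needs no extra pairs or centres. The price is a less favourable stated power and a wider confidence interval.

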4. Analysis of secondary effectiveness. To evaluate the effect of the educational group intervention on the duration of the different types of breast-feeding, an analysis of survival will be done, making the comparison between the two groups using the log-rank test. The control of the possible confounding variable will be done with the construction of different Cox regression models. The proportion of women that attend at least 85% of the planned sessions will be calculated to study the degree of adherence. The women’s satisfaction with the educational group intervention will be measured with a Likert-type scale.

All *p*-values below 0.05 will be considered as statistically significant for all cases.

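### The stated 5% type I error and 80% power come from an uncorrected chi-squared formula and are not jointly delivered by the named primary test, Fisher's exact test, in this clustered design

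*Protocol article*

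**What the plan says.** The Sample size section of the protocol article gives these inputs: "Assuming that 24% of mothers use EBF at six months"; the intervention "can increase the proportion of mother/infant pairs that use EBF at six months by 15" per cent; and, with "a type I error of 5% and a strength of 80%, we need a sample of 150 mother/infant pairs in each group". It names no test, formula or sidedness. A design effect of 1.29 (30 pairs per centre, intraclass correlation 0.01) raises 150 to 194 per group, and a 10% loss allowance raises that to 216.

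Item 3 of the Statistical analysis section fixes the primary comparison: the "proportion of mother/child pairs using EBF at six months in both groups, using Fisher’s exact test". Logistic regression follows only if confounders turn out to be unevenly distributed. The opening paragraph of that section promises that the cluster design will be allowed for throughout, including in hypothesis tests, but attaches no method to the primary test. The significance rule is that "values below 0.05 will be considered as statistically significant for all cases".

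The Design section gives ten centres, and the Randomisation section says the groups are to be of equal size. That makes five centres per arm.

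**The concern.** The power statement and the primary test are both fixed in this document, but they describe different procedures. The calculation uses a large-sample chi-squared formula for independent pairs and then inflates the result for clustering. The test is an exact test on individual pairs that makes no use of the centres.

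Two things are at stake. If the test is run as written, a p-value below 0.05 will occur too often when there is no effect. If the test is replaced by one that respects the centres, the 80% no longer applies, and a null result would be read against a power the trial does not have.

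**Working it through.** **Inputs.** Control 24%; intervention 39% (15 read as percentage points); 5% error; 80% power; design effect 1.29; 10% loss; intraclass correlation 0.01 (all Sample size section). Ten centres, five per arm (Design and Randomisation sections). Two-sided testing is assumed because the document does not state it.

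**1. Reproduce the plan's figure.** With mean proportion 0.315:

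n = [1.96 × √(2 × 0.315 × 0.685) + 0.8416 × √(0.24 × 0.76 + 0.39 × 0.61)]² / 0.15²
= [1.96 × 0.6569 + 0.8416 × 0.6483]² / 0.0225 = 149.4, rounded up to **150**.

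Then 150 × 1.29 = 193.5, up to 194, and 194 / 0.9 = 215.6, up to 216. The plan's chain is reproduced exactly.

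Alternatives support this reading:
- Other uncorrected two-sided formulas give 147 to 151.
- The continuity-corrected formula, which approximates Fisher's test, gives 163.
- One-sided testing gives 118.
- A relative increase of 15% (24% to 27.6%) would need 2318 per group.

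**2. Fisher's test on independent pairs.** All outcomes of two binomials were enumerated, rejecting when the two-sided Fisher p-value is at most 0.05.

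| Pairs per arm | Power, 24% v 39% |
|---|---|
| 150 | 76.9% |
| 161 | 79.8% |
| 162 | 80.1% |

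The actual type I error at 150 per arm is 3.7% (common rate 24%) to 3.8% (common rate 31.5%). With the Background section's other baseline rates, 23.54% and 24.72%, each plus 15 points, power at 150 is 77.3% and 76.3%.

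**3. Fisher's test as written, on the planned clustered data.** The test will be run on about 194 analysed pairs per arm, not on 150 independent ones. I simulated centre-level rates from a beta distribution with intraclass correlation 0.01, using five centres per arm (four of 39 pairs and one of 38) and 400,000 trials, and applied ordinary Fisher's test to the pooled counts.

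| Quantity | Result |
|---|---|
| Power, 24% v 39% | about 83% |
| Type I error, common rate 24% | about 7.7% |
| Type I error, common rate 31.5% | about 7.8% |

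With seven centres per arm of 27 to 28 pairs, nearer the assumed average of 30, power is about 84% and type I error about 6.6%.

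**4. A test that allows for centres.** Cluster-level t-test, five centres per arm, 194 / 5 = 38.8 pairs per centre:

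- Design effect: 1 + 37.8 × 0.01 = 1.378.
- Variance of the difference: (0.1824 + 0.2379) × 1.378 / 194 = 0.002985; standard error 0.0546.
- Non-centrality: 0.15 / 0.0546 = 2.75 on 8 degrees of freedom.
- Power: **about 67%**.

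The simulation in step 3 gives the same 67%, with type I error 5.0%.

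**The case against.** The strongest reply is that nothing is miscalculated, and that planning with a normal-approximation formula is ordinary practice. That stands as far as it goes: the arithmetic is right, and a 3-point difference on independent pairs is small beside a conjectured 15-point effect and an assumed intraclass correlation of 0.01.

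A second reply is that the test will use 194 pairs per arm, not 150. This is also correct, and it matters. A reader might infer that Fisher's conservatism leaves the trial at 77% power, or at 74% if 194 is first divided by 1.378 to give about 141 effective pairs, and that the target should rise from 216 to about 233 per arm (162 × 1.29 = 209; 209 / 0.9 = 232.2). The documents do not support that. The 77% and the conservatism hold only for independent pairs. The 74% applies Fisher's test to a deflated sample that no analysis in the plan would use. On the planned clustered data, Fisher's test exceeds 80% power and is anti-conservative.

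A third reply is that the general promise to allow for clustering means plain Fisher's test is not intended. On that reading the power shown in step 2 is irrelevant. But the primary analysis then has no named test, and the stated 80% has not been shown for whatever replaces it. With ten centres, a cluster-level t-test falls well short of it.

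**Conclusion.** The point holds as a mismatch between the stated operating characteristics and the named test. On independent pairs, Fisher's test has about 77% power with type I error below 5%. Run as written on the planned clustered sample, it has about 83% power with about 7.7% type I error. A cluster-level t-test holds 5% but has about 67% power. None of these gives the stated pair of 5% and 80%.

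It should not be read as a finding that Fisher's test is too conservative here or that more pairs are required. The larger part of the problem is that the named test ignores the centres.

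The figures assume two-sided testing, 24% against 39%, near-equal centre sizes, 194 analysed pairs per arm in five centres per arm, and the plan's intraclass correlation of 0.01. The source formula is inferred, because the document names none, but the exact match at 150 makes the inference strong.

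**What to change.** In item 3 of the Statistical analysis section, replace Fisher's exact test with a comparison that allows for centres: either a cluster-level test or a cluster-adjusted model suited to ten centres. This brings the item into line with the section's own opening commitment. In the Sample size section, name that test, state that it is two-sided, and restate its power for ten centres. For a cluster-level t-test with five centres of about 39 analysed pairs per arm at intraclass correlation 0.01, that is about 67%.

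Do not keep Fisher's test with a restated 77%: that would retain an inflated type I error and attach a power figure that does not apply to clustered data.

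The cost is a change of wording in two paragraphs and a less favourable stated power. No additional pairs are requested.

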### Randomisation

The randomisation unit will be the healthcare centres.

An independent statistician will carry out the randomised allocation to form groups of the same size from a list of the participating healthcare centres.

Posteriorly, within each unit, the mother-infant pairs will be selected by consecutive sampling, until the number is reached to form the cluster. Figure 1 describes how the pairs are recruited. During the consultations, the mothers will be informed about the study and asked if they would like to participate. All mothers that would like to have to sign a consent form and it will be confirmed that they meet all inclusion/exclusion criteria.

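### The design effect of 1.29 rests on 30 pairs per centre, which does not fit ten centres and 432 pairs; on the protocol's own formula, power is about 78%, not 80%

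*Protocol article*

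**What the plan says.** All references are to the protocol article.

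- **Design of the study** fixes the number of clusters: "The intervention will be carried out with mother-infant pairs in ten PHCCs in the Community of Madrid (Spain"). Under Randomisation, the centres are split into two groups of equal size, so five per arm.
- **Sample size** starts from the control rate, "Assuming that 24% of mothers use EBF at six months", and an intervention that "can increase the proportion of mother/infant pairs that use EBF at six months by 15"%. It then states: "a type I error of 5% and a strength of 80%, we need a sample of 150 mother/infant pairs in each group".
- The same section inflates for clustering by 1 + (ñ − 1) × CCI, "where ñ is the average size of each cluster and CCI is the intra-class coefficient of correlation", and continues: "Considering a CCI of 0.01 and an average size of 30 pairs per centre, the effect of the design is 1.29". This gives 194 per group.
- After a 10% loss, "the total size surpasses 432 pairs (216 for each branch"). The Abstract repeats 432 and 216.
- **Randomisation** says that pairs are taken consecutively in each centre "until the number is reached to form the cluster". It does not give that number.

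**The concern.** The number of centres, the pairs per centre and the total are tied together by multiplication, and the three stated values do not multiply out. The design effect depends directly on the pairs per centre. If the true cluster size is larger than the one used, the inflation is too small and the stated 80% power is not reached with 432 pairs.

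There is also a practical side. Recruitment in each centre ends at a number that the Randomisation section leaves open, and the only per-centre figure anywhere in the text is 30.

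**Working it through.** **Inputs.** Control 24%, intervention 39%, type I error 5% (two-sided reproduces the stated figure), power 80%, intra-class correlation 0.01, 30 pairs per centre, loss 10%, total 432: all from Sample size. Ten centres: from Design of the study. Five per arm: from the equal groups under Randomisation.

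**1. The protocol's own chain reproduces.**
- Unadjusted size, pooled variance under the null, mean proportion 0.315: n = [1.96 × √(2 × 0.315 × 0.685) + 0.8416 × √(0.24 × 0.76 + 0.39 × 0.61)]² / 0.15² = 149.4, so 150 per arm. Reading the 15% as relative would need 2318 per arm, so the absolute reading is the intended one.
- Design effect: 1 + 29 × 0.01 = 1.29.
- 150 × 1.29 = 193.5, so 194; 194 / 0.9 = 215.6, so 216 per arm and 432 in total.

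**2. The three figures do not fit.**
- 10 × 30 = 300 pairs, not 432.
- 432 / 10 = 43.2 recruited per centre; 43.2 × 0.9 = 38.88 analysed.
- 432 / 30 = 14.4 centres.

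**3. Design effect and power for ten centres and 432 pairs.** Power = Φ{[0.15 × √n_eff − 1.96 × √0.43155] / √0.4203}, with n_eff = analysed pairs per arm / design effect.

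| Case | Analysed per arm | Cluster size used | Design effect | Effective n per arm | Power (normal) |
|---|---|---|---|---|---|
| As stated | 194 | 30 | 1.29 | 150.4 | 80.3% |
| Ten centres, analysed size | 194.4 | 38.88 | 1.379 | 141.0 | 77.7% |
| Ten centres, recruited size | 194 | 43.2 | 1.422 | 136.4 | 76.3% |
| Ten centres, no losses | 216 | 43.2 | 1.422 | 151.9 | 80.7% |
| Ten centres of 30, 10% loss | 135 | 27 | 1.26 | 107.1 | 65.9% |

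**4. Size that would give 80% with five centres per arm.** The cluster size grows with the sample, so it must be solved together with the design effect: N = 150 × [1 + (N/5 − 1) × 0.01]. Hence N = 150 × 0.99 / (1 − 150 × 0.01 / 5) = 148.5 / 0.7 = 212.1 analysed per arm, and 212.1 / 0.9 = 235.7, so 236 recruited per arm (472 in total). Check: 212.1 / 5 = 42.4 per centre, design effect 1.414, 212.1 / 1.414 = 150.

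**5. A separate matter: few clusters.** The figures above use normal quantiles. With ten centres, a t reference has 10 − 2 = 8 degrees of freedom. A noncentral t calculation with unpooled variance gives about 67% at effective n 141, and about 70% at the protocol's own design effect of 1.29.

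**The case against.** **The arithmetic is not faulty.** This stands. 1.29 is exact for 30 pairs, and every later step follows. The fault is one input that does not match the planned number of centres.

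**The effect on power is small and depends on losses.** This also stands. The mismatch alone costs about 2.6 points (80.3% to 77.7%), and with no losses power would be 80.7% even at a design effect of 1.42. But the 10% loss is the protocol's own planning assumption, so the power it states has to allow for it.

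**Ten centres might mean ten intervention centres.** The sentence can be read that way, less naturally, giving 20 centres in all. Then there would be 21.6 recruited or 19.4 analysed pairs per centre, a design effect of about 1.18 to 1.21 and power of about 83% to 84%. The figure of 30 would still be wrong, but power would not be short. The sentence describes the trial as a whole, so ten in total is the plain reading. The project structure figure is not available to settle it.

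**Two stronger readings are tempting and not supported.**
- A reader might infer that the cluster-size mismatch pulls power down to about 67%. It does not. Most of that fall comes from the 8-degree-of-freedom reference, which gives about 70% even at 1.29. The Statistical analysis section names Fisher's exact test and logistic regression, with the cluster design taken into account. It does not name a centre-level t analysis.
- A reader might infer that centres will stop at 30 and leave the trial 132 pairs short. The text calls 30 an average, sets no quota, and gives the total as 432 in two places. The 66% is what would follow if 30 were used as the quota, not what the protocol plans.

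**Conclusion.** The point holds in a limited form. Ten centres, 30 pairs per centre and 432 pairs are incompatible, and the design effect of 1.29 belongs to a cluster size that the design does not have. Under the protocol's formula, its intra-class correlation of 0.01 and its 10% loss, the design effect is 1.38 (1.42 on recruited numbers), the effective sample is about 141 per arm instead of 150, and power is about 78% (76%) instead of 80%.

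This rests on ten centres in the whole trial, equal cluster sizes and the normal approximation that the protocol's own figure implies. The loss of power is modest. It still merits correction, because the power claim for the primary outcome depends on it and the open per-centre recruitment number makes the inconsistency a practical one.

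**What to change.** - Reconcile Design of the study, Sample size and Randomisation to one set: number of centres in the whole trial, pairs per centre, and total.
- If ten centres and 432 pairs stand, compute the design effect on the analysed cluster size (about 39 per centre, 1.38), say that this is the size used, and restate power as about 78%.
- Put the per-centre recruitment number (about 43 to 44) into Randomisation, so that 30 cannot be taken for the quota.
- Say which reference the restated power uses. If the test allows for only ten clusters (8 degrees of freedom), the figure is nearer 67%.

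The cost is a text correction and a less favourable stated power; restating needs no extra pairs. Keeping 80% on the normal approximation with five centres per arm would be a different choice, at about 236 recruited per arm (472 in total, 40 more than planned).
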